**6. Who should not take Mifeprex? (select all that apply)**

- ☐ A woman seeking an abortion for an ectopic pregnancy
- ☐ A woman who is 3 weeks' pregnant
- ☐ A woman who is 10 weeks' pregnant
- ☐ A woman who is currently using an IUD
- ☐ Unable to locate information

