## 2.0 Background

In Fall 2023, FDA proposed amending its current prescription drug labeling regulations to facilitate patient decision-making. It would require drug companies to provide patient medication information (PMI) in a new template. FDA proposed a one-page document that highlights the “essential information that patients need to know about the prescription drug product, including basic directions on how to use the product safely and effectively.” When evaluating drugs for approval, FDA uses a Benefit-Risk Framework (BRF). The BRF considers risks, benefits, and alternatives for a drug. FDA references the BRF as guiding development of the new PMI, which largely aligns with the BRF. However, the current proposal does not contain information regarding a drug’s *benefit*, thereby omitting critical information for patients’ decision-making. FDA’s proposal also does not include any quantitative estimates of the medication’s risks or benefits, which decision science research has demonstrated that people utilize in their decision-making process. Additionally, the proposal does not require user testing of PMIs.

We aim to address these issues by (a) extending the proposed PMI to include benefit information and quantitative information about safety and effectiveness and (b) demonstrating a simple procedure for user testing. Using Mifeprex (generic: Mifepristone) as a case study, we demonstrate the procedure with a medication that is FDA-approved, safe, and effective medication for abortion and miscarriage management up to 10 weeks’ gestation.

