### *Vendor PMI (control)*

This patient medication information format is the current standard of care patient medication information that is included with the drug. No drug or device is included as part of this intervention.

**Primary outcome.** Participants responses will be evaluated in the following domains:

Usefulness of Information

*Readability*

- Single question with a 5-point Likert scale response for "How easy or difficult was it to read the medication information guide about Mifeprex?" Minimum score is 1; Maximum score is 5. A higher score represents higher perceived readability.

*Supports Decision Making*

- Single question with a 5-point Likert scale response for "For someone who had not yet decided to use Mifeprex, how useful would the medication information guide be in helping them to make that decision?" Minimum score is 1. Maximum score is 5. A higher score represents higher perceived usefulness.

*Supports Proper Use*

- Single question with a 5-point Likert scale response for "If someone had decided to use Mifeprex, how useful would the medication information guide about [drug] be in helping them use the drug properly? " Minimum score is 1. Maximum score is 5. A higher score represents higher perceived usefulness.

Comprehension

- 10 newly constructed questions designed to measure the comprehension of the following information from the medication information guide: 1) Analysis of condition (1 question) 2) Risks (3 questions) 3) Risk Management (3 questions), and 5) Benefits (3 questions). Participants can score from 0-10 with 10 representing full comprehension of the information and 0 representing no comprehension of the information. Comprehension questions will be divided into two scores: *Knowledge Common to All PMIs* (Appendix 3 #1, 2, 6-10) and *Quantified Risk/Benefit Knowledge* (Appendix 3 #3-5).

Perceptions of Regulatory Data

*Strength of Evidence*

- Single question with a 5-point Likert scale response for "In your opinion, how strong is the *scientific evidence* that

134 Mifeprex, when taken correctly, helps patients end an early  
135 pregnancy?" Minimum score is 1; Maximum score is 5. A  
136 higher score represents stronger perceived evidence.

137 *Drug Safety*

- 138 ○ Single question with a 5-point Likert scale response for "In  
139 your opinion, how *safe* is Mifeprex, when taken correctly, for  
140 ending an early pregnancy?" Minimum score is 1. Maximum  

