175 each group to have at most a high school education. Other characteristics  
176 should be similarly distributed across study groups.

177 Based on response variance in our pilot study, a sample size of 100  
178 participants per condition will yield statistical power with at least 85%  
179 chance of detecting a 0.5-point difference in comprehension (with a  
180 minimum score of 0 and maximum score of 7) between the *FDA PMI* and  
181 *Vendor PMI* group, assuming a two-sided  $\alpha = .05$ .

182 We hypothesize that the *FDA PMI* and *Decision Critical PMI* will be  
183 perceived as more readable and demonstrate greater comprehension than  
184 the *Vendor PMI*, as these formats are designed with readability and  
185 comprehension in mind. Additionally, we anticipate the *Decision Critical*  
186 *PMI* will be rated as more useful in supporting decision-making than the  
187 other two PMI formats. We do not anticipate differences in supporting  
188 proper drug use since supporting use is the primary goal of the *Vendor* and  
189 *FDA PMI* formats.

190 All analyses will be conducted using R Statistical Software (v4.3.2).

191 **Ethical considerations.** This study received expedited review and  
192 approval by Carnegie Mellon University's Institutional Review Board  
193 (STUDY2023\_00000449). The study protocol was registered on  
194 ClinicalTrials.gov (NCT06320808) and followed the Consolidated  
195 Standards of Reporting Trials (CONSORT) guidelines.

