**1. What is Mifeprex used for?**

- ☐ To end an early pregnancy, up to 6 weeks
- ☐ To end an early pregnancy, up to 10 weeks
- ☐ To end a pregnancy in the first or second trimester
- ☐ To end a pregnancy at any time before delivery
- ☐ Unable to locate information

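### Item 6 of the seven-item comprehension score the trial is sized on has a response option at the ten-week limit, so some readers who understood the guide may be marked wrong

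*Protocol*

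**What the plan says.** Section 2.0 (Background) describes the drug as a "effective medication for abortion and miscarriage management up to 10 weeks" of gestation. In Appendix 3, item 1 (what the drug is used for), the only response that matches this is "To end an early pregnancy, up to 10 weeks".

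Item 6 of Appendix 3 is a multiple-response question: "Who should not take Mifeprex? (select all that apply". It has four substantive options: an ectopic pregnancy, a pregnancy of 3 weeks, current IUD use, and "A woman who is 10 weeks' pregnant".

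Section 6.0 (Primary outcome, Comprehension) splits the ten questions into two scores. The common-knowledge score is made up of "Appendix 3 #1, 2, 6-10", which includes item 6. The power statement in the same section refers to a "chance of detecting a 0.5-point difference in comprehension (with a" "minimum score of 0 and maximum score of 7) between the *FDA PMI* and" Vendor PMI groups, with 100 participants per condition, at least 85% power and a two-sided alpha of .05.

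The survey introduction in Appendix 3 tells participants that the guide stays visible beneath each question.

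**The concern.** Two ambiguities meet in one option. *Up to* ten weeks can include or exclude the limit itself. A woman described as ten weeks pregnant may be at exactly ten weeks or at any day of that week. If the guide in front of the reader says no more than the Background does, both answers to this option are defensible, and whichever way it is keyed, one of them is marked wrong. The survey is open-book, so going back to the guide does not help a reader whose guide is no more precise.

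The item counts towards the comprehension score used for the sample size. Correct understanding scored as error dilutes the contrast between guides. If it happened more often in one arm, it would also shift the contrast.

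**Working it through.** **1. Is item 6 in the powered score?** The common-knowledge items are 1, 2, 6, 7, 8, 9 and 10, which is seven. The power statement's range is 0 to 7. The two match, so item 6 is in the score on which the trial is sized.

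**2. Where does the option fall?** The Background and item 1 both put the limit at ten weeks, with no days and no statement of whether the limit is included. Item 6 uses the same number, also without days. The other gestation offered, 3 weeks, is well inside the limit. Only the ten-week option coincides with it.

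**3. What can one respondent lose?** Ten questions scored 0 to 10 suggests one point each. Under all-or-nothing scoring, one disputed option costs up to 1 point. Under partial credit it costs a fraction; for example, with the four substantive options weighted equally, 1/4 = 0.25 point. The protocol does not say which rule applies.

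**4. The plan's own power figure.** The pilot SD is not given, so 85% cannot be checked independently. Solving for the SD it implies, by the normal approximation for two means (the planned test is Mann-Whitney, so this is approximate):

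SD = 0.5 / [√(2/100) × (1.960 + 1.036)] = 0.5 / (0.1414 × 2.996) = 1.18.

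**5. Equal mis-scoring in both arms.** Assumptions: SD stays at 1.18; the 0.5-point effect is spread evenly over the seven items, 0.5/7 = 0.0714 each; scoring is all-or-nothing; and a share m of understanding readers is marked wrong on item 6 in each arm. The expected difference becomes 0.5 − 0.0714 × m.

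| m | Difference | Power |
|---|---|---|
| 0 | 0.500 | 85.0% |
| 10% | 0.493 | 84.0% |
| 25% | 0.482 | 82.4% |
| 50% | 0.464 | 79.5% |

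No value of m is in the protocol, so the table shows sensitivity and is not an estimate.

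**6. Unequal mis-scoring.** Under all-or-nothing scoring, the shift in the arm difference would be c × g × 1 point. Here c is the share of readers otherwise correct on item 6, and g is the between-arm difference in the share of those readers who are mis-scored. Neither quantity is in the protocol. As an arithmetic example only, c = 80% with g = 10 or 20 percentage points gives 0.08 or 0.16 point, which is 16% or 32% of the 0.5-point target.

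**The case against.** The strongest reply is that the guides themselves are not reproduced in the protocol. The guide, not the Background, is what the respondent reads, and a guide that states the limit precisely enough, for instance with an explicit rule on who should not take the drug, could settle the option for its readers. This stands, and it is why the point is conditional. It also rules out saying that the option cannot be keyed at all.

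The answer key and the scoring rule for multiple-response items may sit in an analysis plan that is not shown, so their absence is not a finding. That also stands, but the point does not depend on it. A key decides how answers are scored; it cannot remove an ambiguity from the question asked.

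The questions were pretested and revised, and the revised survey was then piloted. If item 6 was in the pilot in this form, its noise is already in the variance used for sizing. That limits the cost further, although the protocol does not say that this option was examined.

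A reader might infer a larger problem: that the guides differ in how they word the limit, so that the item produces a spurious arm difference of 0.1 to 0.3 point, or 20% to 60% of the target. The protocol does not support this. Those figures need a 10 to 30 percentage point difference in misreading, which no passage documents, and they treat every reader as otherwise correct on the item. Comparing the item's one point with the 0.5-point target also misleads, since one is a single respondent's score and the other a difference in group means. Finally, if one guide states the limit more clearly and its readers answer better, part of that is the effect under study.

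**Conclusion.** The point holds as a flaw in item wording, conditional on the guides being no more precise than the Background and item 1. A reader who understood such a guide may lose up to one point of seven, or a fraction of a point under partial credit. With equal misreading across arms the consequence is modest: about 84.0% to 82.4% power in place of 85% if 10% to 25% of understanding readers are mis-scored, given an SD of 1.18, an effect spread evenly over the items, and all-or-nothing scoring. Bias between arms is possible only if the guides word the limit differently, and its size cannot be derived from the protocol. No stated figure is shown to be wrong, and no view is taken on the correct clinical limit.

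**What to change.** Check the wording of the limit in all three guides, then replace the ten-week option in item 6 with a gestation clearly on one side of the limit as printed in each of them. If the survey has already been fielded, score item 6 on the remaining three substantive options (ectopic pregnancy, 3 weeks, IUD) and record that key before unmasking.

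The cost is one edited response option or one line in the scoring key. Item 6 would no longer probe the exact limit, but item 1 already tests whether readers know it.

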**7. Which of the following are common side effects of Mifeprex? (select all that apply)**

- ☐ Headache
- ☐ Fever
- ☐ Hair loss
- ☐ Severe pelvic discomfort
- ☐ Unable to locate information

**8. How can you contact the FDA to report side effects? (if you cannot locate this information, skip to the next question)**

**9. Which of the following should a woman who has taken Mifeprex immediately call their healthcare provider about? (select all that apply)**

- ☐ Bleeding or spotting for 14 days
- ☐ Developing a fever of 101 degrees that lasts all day
- ☐ Having mild abdominal pain
- ☐ Bleeding enough to soak through two pads every hour for three hours
- ☐ Unable to locate information

**10. How long should a woman who has taken Mifeprex expect vaginal bleeding or spotting?**

- ☐ 24 to 48 hours
- ☐ 9 to 16 days
- ☐ 9 to 20 days
- ☐ 10 weeks
- ☐ Unable to locate information

The next set of questions ask your opinion about the drug, Mifeprex, that was described in the prescription medication guide you just saw.

**11. In your opinion, how strong is the *scientific evidence* that Mifeprex, when taken correctly, helps patients end an early pregnancy?**

- ☐ Very weak
- ☐ Weak
- ☐ Neither weak nor strong
- ☐ Strong
- ☐ Very strong

**12. In your opinion, how *safe* is Mifeprex, when taken correctly, for ending an early pregnancy?**

- ☐ Extremely safe
- ☐ Somewhat safe
- ☐ Neutral/Not sure
- ☐ Somewhat unsafe
- ☐ Extremely unsafe

**13. In your opinion, how *effective* is Mifeprex, when taken correctly, for ending an early pregnancy?**

- ☐ Extremely effective
- ☐ Somewhat effective
- ☐ Neutral/Not sure
- ☐ Somewhat ineffective
- ☐ Very ineffective

**14. If you had to end an early pregnancy, would you want to take Mifeprex to do so?**

- ☐ Definitely not
- ☐ Probably not
- ☐ Probably yes
- ☐ Definitely yes
- ☐ Not applicable – I do not support terminating a pregnancy

Thinking about the medication information sheet you saw about Mifeprex...

**15. How *easy* or *difficult* was it to read the medication information guide about Mifeprex?**

- ☐ Very difficult
- ☐ Difficult
- ☐ Neither difficult or easy
- ☐ Easy
- ☐ Very easy

**16. For someone who had not yet decided to use Mifeprex, how *useful* would the medication information guide be in helping them to make that decision?**

- ☐ Extremely useful
- ☐ Useful
- ☐ Neither useful or useless
- ☐ Useless
- ☐ Completely useless

**17. If someone had decided to use Mifeprex, how *useful* would the medication information guide about Mifeprex be in helping them use the drug properly?**

- ☐ Extremely useful
- ☐ Useful
- ☐ Neither useful or useless
- ☐ Useless
- ☐ Completely useless

**18. Is there any other information, not provided on the medication information guide, that would have been helpful to know?**

This study showed information about a medication for abortion. As you may know, on June 24, 2022 the Supreme Court overturned *Roe v. Wade*. This means that each U.S. state can decide its own policy on whether to ban or restrict abortion.

**19. Which of the following best describes your feeling about the Supreme Court's overturning of *Roe v. Wade*?**

- ☐ It is taking our country very much in the right direction
- ☐ It is taking our country somewhat in the right direction
- ☐ I feel neutral/I don't know
- ☐ It is taking our country somewhat in the wrong direction
- ☐ It is taking our country very much in the wrong direction

Lastly, we ask some demographic questions about you. We ask these questions to make sure we are surveying a diverse group of people.

**20. What is your age?**

**21. What sex were you assigned at birth, meaning on your original birth certificate?**

- ☐ Male
- ☐ Female
- ☐ Prefer not to answer

**22. Which of the following best describes your gender identity?**

- ☐ Male
- ☐ Female
- ☐ Non-binary
- ☐ Prefer to Self-Describe (please specify)
- ☐ Prefer not to answer

**23. What is your race and ethnicity? Select all that apply**

- ☐ American Indian or Alaska Native
- ☐ Asian
- ☐ Black or African American
- ☐ Hispanic or Latino
- ☐ Middle Eastern or North African
- ☐ Native Hawaiian or Pacific Islander
- ☐ White
- ☐ Prefer not to answer

**24. Have you or someone you care about ever used the drug described in the medication guide?**

- ☐ Yes
- ☐ No
- ☐ I don't know
- ☐ Prefer not to answer

**25. What is your 5-digit zipcode?**

472

473

474

475

476

**26. If there is anything you would like to share that is not addressed in a survey question, we encourage you to add your comments here.**

